### Participants

A total of 66 community-dwelling participants with MCI will be recruited from community centres for the elderly and Non-Governmental Organizations (NGOs) providing care services to elderly people with cognitive impairment in different districts in Hong Kong. The proposed sample size is calculated using G*power 3.1.9.4, based on a power estimate of 80% with α = .05, an effect size of d = 0.40 (with reference to the averaged effect size of 0.43 on global cognition, as reported in the latest Cochrane Review [9] on cognitive stimulation on PwD), and an attrition rate of 25%. The effect size of cognitive stimulation on PwD ranged from 0.3 to 1.32 [9], while an effect size of 0.564 was reported in adapted CST on MCI [16]. Also, the effect size of previous RCTs using VR on cognitive intervention of MCI ranged from 0.6 to 0.9 on measures of general cognition. Thus, an effect size estimate of 0.4 for the current proposal is considered relatively conservative. The attrition rates of previous VR studies on MCI are considered low (6–14%); thus, the estimated attrition rate of the current proposal is considered modest.

Inclusion criteria include: 1) elderly aged 60 years or above. 2) A score of 16–21 out of 30 in the Hong Kong Brief Cognitive Test [25], with upper and lower cutoff scores for MCI as suggested by the test. 3) ability to speak and comprehend Cantonese; 4) normal or corrected-to-normal vision and hearing; 5) absence of physical illness/disability to prevent them from IVR-CST participation; and 6) compatible with IVR exposure in the 10-minute IVR trial without major signs of cybersickness, based on the symptoms given in the Simulator Sickness Questionnaire [26]. Exclusion criteria include 1) concurrent participation in other clinical therapy trials; 2) incompatibility with IVR exposure such as complaints of nausea, headache, or other severe discomforts during trial use; 3) a diagnosis of dementia or other psychiatric/neurological diseases such as depression, stroke, brain trauma, Parkinson’s disease; 4) hearing/visual/upper limb impairments that hinder CST/IVR-CST participation; 5) prior CST treatment; 6) Use of medication for MCI/dementia, e.g., aducanumab. Screening will be done by a trained research assistant in a quiet room. Participants’ demographic information, medical and family history will be obtained.

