### Assessment and treatment schedule

All participants will be assessed at three time points throughout the study: week 1, week 9, and week 13 to evaluate their performance before, immediately after, and in the maintenance phase, respectively. The treatment schedule will be the same for both treatment conditions, in which 14 therapy sessions will occur twice per week from week 2 to week 8.

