### Data analysis

Primary and secondary outcomes will be scored by a trained research assistant who is not involved in the assessment. To further reduce observer bias, a random code will be given to the scoring forms and audio-recording so that the research assistant will be blind to the identity of the participant, the experimental group assigned, and the timepoint of assessment. A linear fixed-effect model will be used to evaluate the participants’ performance in the outcome measures, as this statistical model is better in handling repeated observations, missing data, and individual variability [33]. Both time points (week 1/9/13) and conditions (IVR-CST vs. conventional CST) will serve as fixed factors, and scores of primary/secondary outcomes as dependent variables. Participants’ characteristics, such as age, baseline cognitive performance, and education, will be included in the model as covariates. Any significant main effects or interactions will be investigated via post-hoc analyses. Measurements concerning feasibility and user experience will be evaluated descriptively. In addition, a narrative summary of responses collected during the post-therapy interview will be reported.

For exploratory outcome, a 5-minute sample will be extracted from each participant and session from the IVR-CST group. To study possible changes in eye movement across sessions, the aforementioned eye-tracking parameters, including number of fixations, duration of fixation, and number of revisits on the AOI generated by each participant, will be evaluated by linear fixed-effect models as dependent variables, with session number as a fixed factor. Any significant main effects will be followed by post-hoc analyses. To investigate the possible associations between eye movement and treatment outcome, the correlation between the averaged difference in number and duration of eye fixations of each participant in the first and last three IVR-CST sessions and the difference score of HK-MoCA before and immediately after therapy will be analysed. If the correlation reaches statistical significance, multiple regression will be conducted, with the eye-tracking parameters as predictors, while the difference score of HK-MoCA pre/post therapy will serve as the predicted variable.

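### Week 1 is a response level while baseline performance is also a covariate, so the adjustment adds no precision to the treatment contrast and a three-visit condition main effect understates the effect

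*Protocol article*

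**What the plan says.** Four statements in the protocol article bear on this point.

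- **Model and responses (Data analysis).** "A linear fixed-effect model will be used to evaluate the participants’ performance in the outcome measures". The section continues: "Both time points (week 1/9/13) and conditions (IVR-CST vs. conventional CST) will serve as fixed factors", with "scores of primary/secondary outcomes as dependent variables".
- **Covariates (same section).** Participant characteristics "such as age, baseline cognitive performance, and education, will be included in the model as covariates". No interaction of a covariate with time is mentioned, and the baseline measure is not defined. It could be the week-1 score of the outcome or the screening score on the Hong Kong Brief Cognitive Test.
- **Timing (Assessment and treatment schedule).** Assessments fall at "week 1, week 9, and week 13 to evaluate their performance before, immediately after, and in the maintenance phase, respectively", and "14 therapy sessions will occur twice per week from week 2 to week 8". Week 1 is therefore pre-treatment.
- **Tests followed up (Data analysis).** "Any significant main effects or interactions will be investigated via post-hoc analyses". No single contrast is named as the treatment estimate.

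**The concern.** The pre-treatment measurement has two roles in the same model: it is one of the three responses, and baseline performance is also adjusted for. A covariate that does not change over visits, with one common slope, shifts all of a participant's expected scores equally. It therefore cannot sharpen a comparison of change from week 1. Listing baseline performance as a covariate suggests a baseline-adjusted comparison, but the model as described does not deliver one for the contrast that answers whether IVR-CST beats conventional CST.

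The condition main effect has a different problem. It averages the arm difference over all three visits, including one where randomization makes the expected difference zero. If that figure were reported as the treatment effect, it would be too small on average.

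**Working it through.** **Inputs.** From the protocol: three visits, with week 1 before therapy; 66 participants at 1:1, so 33 per arm; 25% attrition, so 33 × 0.75 = 24.75, about 25 per arm; and, for the sample size, "based on a power estimate of 80% with α = .05, an effect size of d = 0.40". Assumed: outcome SD of 1 at each visit, an equal correlation r between visits, a two-sided test, and a constant effect of 0.40 at weeks 9 and 13. The protocol gives no r, so a range is shown. It also gives no figure of its own for this contrast to reproduce.

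**Step 1: cancellation.** Write the expected score of a participant in arm g at visit t as m(g,t) + β·b, with b the baseline covariate. The adjusted arm mean at each visit is the raw mean minus β times the arm's mean of b. That term is the same at weeks 1 and 9, so it drops out of (week 9 − week 1), and hence out of the between-arm difference in that change. This holds whether b is the week-1 outcome or the screening score.

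Simulated fits with a random intercept and 33 per arm agree:

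- *Complete data.* The interaction estimate was the same with and without the covariate (largest difference about 1e-14). In one data set at r = 0.5 it was 0.4335 both ways, with SE 0.2255 both ways.
- *25% random dropout after week 1.* Single estimates moved by at most 0.07 to 0.15 SD, depending on r. The mean was practically unchanged (0.384 and 0.386 at r = 0.5). The SE printed by the model fell from 0.274 to 0.255 at r = 0.5. This should not be read as a real gain: a repeat of the check showed the same spread of estimates with and without the covariate. The likely reason is that one residual variance is fitted to visits whose residual variances differ (see the objection).

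**Step 2: precision.** In SD² units the per-participant variance is 2(1 − r) for a change score and 1 − r² for an analysis adjusted for the week-1 score. The ratio is 2(1 − r)/(1 − r²) = 2/(1 + r). The SE of the arm difference is √(2v/n). At n = 25 and r = 0.5 this is √(2 × 1.00/25) = 0.283 against √(2 × 0.75/25) = 0.245. Power at d = 0.40, two-sided 0.05, from the noncentral t:

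| r (assumed) | Variance ratio | SE, change | SE, adjusted | Power, change | Power, adjusted |
|---|---|---|---|---|---|
| 0.5 | 1.33 | 0.283 | 0.245 | 28% | 36% |
| 0.7 | 1.18 | 0.219 | 0.202 | 43% | 49% |
| 0.8 | 1.11 | 0.179 | 0.170 | 59% | 64% |

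**Step 3: main effect.** The average over three visits is (0 + 0.40 + 0.40)/3 = 0.267, which is two thirds of 0.40. Simulation with 33 per arm and complete data gave 0.253, 0.265 and 0.267 at r = 0.3, 0.5 and 0.7. With post-treatment visits only it gave 0.379, 0.397 and 0.401.

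**Step 4: the test of that main effect.** With the week-1 outcome as covariate, complete data and r = 0.5, the three-visit SE was 0.115 and the post-treatment SE 0.173. Estimate and SE shrink together, and the mean test statistic was 2.33 in both.

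**The case against.** The strongest reply is that the common slope is a reading, not a statement. The article neither states nor excludes covariate-by-time terms, and a fuller document might contain them. If the week-1 score were the covariate and baseline-by-time were included, the simulated SE at 25 per arm would be 0.247 (r = 0.5) and 0.207 (r = 0.7), the same as for the adjusted analysis. That stands as a qualification. Even so, the factors and covariates are listed, and the plain reading of the list is one slope per covariate.

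A second reply is that a condition-by-time model with baseline as a response is conventional and unbiased under randomization. That stands in full: the loss is in precision and in correction for chance baseline imbalance.

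Several stronger readings are tempting, but the documents do not support them:

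- *The main-effect test loses a third of its power.* If the covariate is the week-1 outcome, it loses almost none with complete data (step 4). The effect size is understated. The proportional shrinkage was checked only for that covariate.
- *Every reported main effect will be too small.* This is true on average, not for each estimate, and the plan does not name the main effect as its treatment estimate.
- *Week-1 residual variance collapses to nearly zero.* With a common slope of (1 + 2r)/3, it is (1 − 0.667)² = 0.11 at week 1 and 1 − 2(0.667)(0.5) + 0.667² = 0.78 later, at r = 0.5. That is clearly unequal, but not zero. It applies only if the covariate is the week-1 outcome.
- *The sponsor believes that its contrast is baseline-adjusted.* The article lists covariates and makes no such claim.

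**Conclusion.** The point holds as a matter of efficiency and interpretation, not validity. As described, the condition-by-time contrast is an unadjusted change-score comparison, exactly so with complete data and nearly so with dropout. The avoidable cost is modest: about 5 to 8 percentage points of power for r between 0.5 and 0.8, at 25 per arm and d = 0.40. A reader might infer that correcting this would rescue the trial's power. It would not: in every row of the table both analyses stay below 80%.

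A condition main effect that includes week 1 would on average show 0.27 for a constant post-treatment effect of 0.40. This matters because the plan would follow up a significant main effect and names no primary contrast. The power figures rest on the assumed r and on equal variances. The cancellation rests on there being no baseline-by-time term. The two-thirds figure rests on an equal effect at weeks 9 and 13.

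**What to change.** Reword the Data analysis section so that the week-1 score has one role. There are two ways to do this:

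1. **Preferred.** Keep weeks 1, 9 and 13 as responses in a constrained longitudinal model. Give both arms a common baseline mean, enter no baseline-score covariate, and model the correlation between a participant's visits. Age and education can stay. This keeps the within-arm before-after estimates that the Abstract and the research questions call for, and it uses participants who have only week-1 data.
2. **For the between-arm comparison only.** Model weeks 9 and 13 with condition, week, condition-by-week, the week-1 score of the same measure, baseline-by-week, age and education. This drops the week-1 level, so the before-after question needs a separate within-arm analysis.

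Under either option, name the week-9 condition difference as the treatment estimate, and state that a condition main effect including week 1 will not be interpreted. If a baseline covariate is kept, say which measurement it is.

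The cost is a small rewording and no new data, plus the separate within-arm analysis if the second option is chosen.

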### Outcome measures and procedures

Primary outcomes: 1) The Hong Kong Montreal Cognitive Assessment (HK-MoCA; 27). It is a sensitive cognitive measure for MCI [27] and covers different cognitive domains, including visuo-spatial skills, executive functions, attention, memory, language, and orientation. The total score (out of 30) will be used to reflect global cognition; 2) Digit span forward and backward tasks, measures of working memory that predict progression from MCI to dementia [28]; 3) Verbal fluency of semantic category. Verbal fluency, which reflects semantic integrity, cognitive flexibility, and executive function, serves as a sensitive task in detecting MCI [29] and predicting conversion to dementia [30]. The number of items correctly produced in one minute in different semantic categories (animals, fruits, and transportation) will be tested.

Secondary outcomes: 1) Chinese version of the Modified Barthel Index [31], which assesses one’s level of independence in activities of daily living such as grooming, feeding, mobility, toileting, etc.; 2) The Hong Kong Lawton Instrumental Activities of Daily Living Scale [32], which evaluates the level of independency in performing community-living skills including cooking, household management, shopping, etc.

Feasibility outcome and users’ experience: Objective and quantifiable feasibility outcomes, including the number of adverse events and technical issues that occurred during intervention, and the level of adherence (actual duration and number of sessions conducted vs. scheduled) to the intervention protocol of both treatment groups, will be measured. Participants of the IVR-CST group will also attend a 20-minute semi-structured interview conducted post-therapy on topics including levels of comfort, presence of adverse effects such as cybersickness, and impact of therapy on daily functions.

Eye-tracking data obtained from the IVR-CST group will serve as an exploratory outcome. In each of the sessions, areas of interest (AOI) of the stimuli presented will be identified. For example, the childhood snacks or toys presented in the themed session ‘Childhood’ will be regarded as AOI. Parameters, including the number of fixations, duration of fixation, and number of revisits on the AOI generated by each participant, will be recorded in the HMD.

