### Treatment materials and procedures

In the IVR-CST group, a total of 14 IVR-CST sessions will be carried out twice per week, with each session lasting about 45 minutes. Therapy will take place in a quiet room in the community elderly centres. A research personnel who is a healthcare professional (e.g., occupational or speech therapist) with a certified CST facilitator qualification will be the group facilitator, and three to four participants with MCI will receive IVR-CST as a group throughout the sessions. An assistant will also be present to provide help if necessary. Treatment instruments will include commercially available HMDs with eye- and hand-tracking functions available (e.g., Meta Quest Pro) for each participant. Treatment materials (i.e., content to be delivered in each themed session) will be adapted from the Chinese-translated manual of CST [11]. Materials presented via HMD will include commercially available VR games suitable for the elderly, photo-real panoramic (i.e., 360-degree) images or videos, and two- or three-dimensional animated images and photos. Use of hand controllers or hand movement will be allowed in some activities, such as physical games or manipulation of 3D objects. Similar to the original CST manual, two activities with varying levels of difficulty will be available to allow some flexibility. The major difference between the level of difficulty of the currently proposed vs. the existing manual lies in the complexity of the tasks or the use of less familiar stimuli. For example, in session 10 ‘Orientation’. The original manual suggests the use of familiar local places as stimuli for discussion; in IVR-CST, less familiar places like overseas tourist spots will be introduced. Sample themed activities are given in Table 1. Treatment procedures will follow the Chinese-translated manual of CST [12]. In the first 10 minutes, participants and the facilitator will greet and meet, and sing-along a group song or share some snacks/drinks. Reality orientation will be followed by telling the participants the time, weather, and recent news/affairs. Then the facilitator will assist the participants to wear the HMD for about 30 minutes, during which the themed activity will be conducted. All participants will be seated comfortably and at a distance far enough from one another to ensure safety during hand movement during IVR exposure. According to the IVR-CST manual, the facilitator will guide the participants to conduct a range of activities, discussions, or sharing. Material presentation will be controlled by the facilitator via a laptop. S/he will not wear an HMD so that immediate assistance to the participants can be provided. In the last five minutes, the HMD will be taken off while the facilitator will round up the session. In the conventional CST group, the same treatment activities, materials, and procedures will be used, while photos, pictures, or real objects will be presented.

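### Session number in the eye-tracking model cannot be separated from session content, and the follow-up regression is reported only when the correlation is significant

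*Protocol article*

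**What the plan says.** All references are to the protocol article.

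- *Outcome measures and procedures* makes eye-tracking an exploratory outcome, collected in the IVR-CST arm only. AOIs are set session by session: "In each of the sessions, areas of interest (AOI) of the stimuli presented will be identified". The example given is the snacks and toys of the Childhood session.
- The Introduction describes CST as having different themed activities in each session. Table 1 links sessions 1, 2, 6 and 9 to physical games, sound, faces/scenes and categorizing objects. *Treatment materials and procedures* links session 10 to orientation.
- The same section says of difficulty that "two activities with varying levels of difficulty will be available to allow some flexibility".
- *Data analysis* takes a 5-minute sample per participant and session. It models number of fixations, fixation duration and revisits "with session number as a fixed factor", with post-hoc analyses of any significant main effect.
- It then correlates the change in number and duration of fixations, first three against last three sessions, with the pre/post change in HK-MoCA. The final step is conditional: "If the correlation reaches statistical significance, multiple regression will be conducted, with the eye-tracking parameters as predictors".

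**The concern.** The session model is there to show whether eye movements change over therapy. If what is on display changes whenever the session number changes, a significant effect may reflect only different stimuli. Session 1 is built on movement games and session 2 on sound. There is no reason to expect the same fixation counts on their AOIs, even from a person whose gaze behaviour has not changed. Because eye-tracking exists in one arm only, no comparison group can remove the content effect.

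The second issue is the conditional regression. A regression reported only after a significant correlation in a small sample is seen only when the observed association happens to be large. The introduction presents eye-tracking as a possible marker of treatment response, so an exaggerated coefficient could be carried into the design of later work.

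**Working it through.** **The plan's own figure.** The only sample-size calculation is for global cognition: "based on a power estimate of 80% with α = .05, an effect size of d = 0.40", with 25% attrition, giving 66. A two-sided paired t-test at d = 0.40 needs 52, and 52 × 1.25 = 65, which is 66 when rounded up to an even number. This supplies the arm size (66 / 2 = 33) but is no basis for the correlation, for which no figure is stated.

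**Step 1: session and theme.** Suppose each of the 14 sessions has its own theme. The 14 session indicators and 14 theme indicators are then the same columns, and the combined matrix has rank 14, not more. Adding a linear session trend to the theme indicators also leaves rank 14. Neither a larger sample nor a random effect separates the two. All 14 × 13 / 2 = 91 possible post-hoc session pairs are theme contrasts as well.

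**Step 2: the change score.** Write participant i's last-three minus first-three difference as D_i = c + d_i + u_i. Here c is the content shift common to everyone, d_i is real change, and u_i is the person's or group's own reaction to the content, including any difference in the level used. Correlation ignores constants, so c drops out. If u_i is unrelated to d_i and to HK-MoCA change, it weakens the correlation by the factor √[var(d) / (var(d) + var(u))]. If it is related to HK-MoCA change, it biases the correlation in either direction.

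**Step 3: the significance condition.** At most 33 participants contribute. After the planned attrition, 33 × 0.75 ≈ 25 do. At the upper attrition rate cited from earlier VR studies (14%), 33 × 0.86 ≈ 28 do.

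Critical value (two-sided 5%): r_c = t / √(n − 2 + t²).
- n = 33: 2.040 / √(31 + 4.16) = 0.344
- n = 25: 2.069 / √(23 + 4.28) = 0.396

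Power by Fisher's z: Φ(atanh(r) × √(n − 3) − 1.96). For r = 0.3, atanh(r) = 0.3095.
- n = 33: Φ(1.695 − 1.960) = 0.40
- n = 25: Φ(1.452 − 1.960) = 0.31

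| n | critical r | power, r = 0.3 | r = 0.4 | r = 0.5 | r needed for 80% power |
|---|---|---|---|---|---|
| 33 | 0.344 | 40% | 64% | 85% | 0.47 |
| 28 | 0.374 | 34% | 56% | 78% | 0.51 |
| 25 | 0.396 | 31% | 51% | 73% | 0.535 |

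Simulation of bivariate normal data agrees. With a true r of 0.3, the mean r among significant results is 0.45 (n = 33) or 0.50 (n = 25). With a true r of 0.5 it is 0.53 or 0.56, so the exaggeration is then small.

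**Step 4: without the condition.** An observed r of 0.3 would carry a 95% CI of about −0.05 to 0.58 (n = 33) or −0.11 to 0.62 (n = 25). That is wide, but not selected.

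**The case against.** The strongest reply is that the hypothesis concerns association, and association is tested by the between-person correlation, not by the session model. That stands. A reader might infer from the confounding that the third hypothesis cannot be answered at all. The documents do not support this, since a shift common to everyone leaves the correlation untouched.

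Other parts of the defence also stand:

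- **Level choice.** It is tempting to say that abler groups receive harder material and so show a different change. The article says only that two levels are available. It does not say how they are chosen or whether they differ between groups. Bias by this route is a possibility, not a finding.
- **Number of themes.** Only five themes appear with a session number, and Table 1 is presented as a selection. Fourteen distinct themes is a reasonable inference from the description of CST, not a documented count.
- **Reporting.** The correlation is analysed whatever its result, so the primary estimate of association is not selected. Only the regression is.
- **Power.** Calling the correlation underpowered depends on the assumed r. At r = 0.5 with all 33 retained, power is 85%. The Discussion already concedes that the sample is small.
- **Raw or normalised measures.** The article does not say which. An article may leave that detail elsewhere, so it is not counted as an error here. The fixed 5-minute sample already equalises observation time.

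The exploratory label lowers the stakes but does not remove the problem. Association with outcome is a listed research question, and the session model and the conditional rule are stated choices, not omissions.

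**Conclusion.** The point holds in limited form. Session-number effects and their post-hoc contrasts are confounded with content and must not be reported as change over therapy. This is structural to the extent that each session carries its own theme, which the article indicates but does not list in full. The correlation survives a shared content shift. Its change score remains open to noise, and possibly bias, from individual reactions to themes and from any variation in level, by an amount the documents do not allow one to estimate.

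The significance condition selects the regression estimates. At an assumed true r of 0.3, they would appear in about 31% to 40% of trials, and the accompanying r would average 0.50 to 0.45 instead of 0.3. These figures take 25 to 33 participants, a two-sided 5% test and a single correlation. The plan names two eye-movement measures and does not say which opens the regression. For an exploratory outcome this is worth correcting, but it does not threaten the trial's main comparison.

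**What to change.** In *Data analysis*:

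1. State that session effects on eye movements are descriptive and confounded with theme, and will not be interpreted as change over therapy.
2. Express AOI measures as a share of all fixations or of dwell time within the 5-minute sample. This reduces dependence on overall gaze activity but does not remove the confounding.
3. Record the difficulty level used in each session, so that variation at either end of the change score can be examined.
4. Drop the significance condition. Fit one pre-specified regression whatever the correlation shows: week-9 HK-MoCA on baseline HK-MoCA and the named eye-tracking change measures, reported with 95% CIs.

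Items 1, 2 and 4 need only wording and data processing; item 3 is one field in the session log. A short standard scene repeated in early and late sessions would break the confounding. It should be regarded as optional, because repeated viewing brings familiarity effects and it takes session time in the IVR-CST arm only, where the plan otherwise keeps the two arms' activities alike.

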
### Eye-tracking in IVR: A biomarker for treatment response?

The application of IVR may go beyond from treatment delivery to investigation of treatment response. Recent technological advancement has enabled reliable and accurate eye-tracking in commercially available HMDs, which allows researchers to explore such applications in theoretical and clinical perspectives. Eye-tracking is a technology which captures distinct eye movement types. For example, in saccadic eye movements in which the eyes scan the visual field via successive eye movements, the eyes will fixate on a certain area of interest for 200–300 ms before moving again. Hence, eye movements such as the position, number, and duration of fixations can be traced via an eye-tracker. According to a recent review on applications of eye-tracking in VR, some of the clinical applications included diagnosis and treatment of neurodegenerative disorders, measurement on visual attention, evaluation of cognitive effort, and as well as evaluation of learning outcomes [23]. Eye-tracking can be regarded as an effective way to detect cognitive decline in people with dementia/MCI [24] As such, eye-tracking seems to be a viable means to investigate the eye movements of PwD/ people with MCI during VR-based therapy, e.g., to examine whether the participant is paying enough attention to the details of the stimuli presented. Furthermore, based on previous studies on healthy adults that the average duration of fixation and the number of revisits successfully predicted learning outcomes [23], one may question if there is a causal relationship between changes in eye movements and treatment gain in MCI population. Nevertheless, this hypothesis has rarely been investigated.

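### The exploratory link between eye-movement change and HK-MoCA change names no person-level covariates, so it cannot separate eye movement from age, education or baseline cognition (minor)

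*Protocol article*

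**What the plan says.** The Data analysis section of the protocol article describes two kinds of model.

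- **Primary and secondary outcomes.** A linear model has time point and condition as factors, "and scores of primary/secondary outcomes as dependent variables". For this model, "Participants’ characteristics, such as age, baseline cognitive performance, and education, will be included in the model as covariates".
- **Exploratory eye-tracking outcome, IVR-CST arm only.** The eye-tracking parameters "will be evaluated by linear fixed-effect models as dependent variables, with session number as a fixed factor". The association with treatment outcome is then examined in two steps. The first is "the correlation between the averaged difference in number and duration of eye fixations of each participant in the first and last three IVR-CST sessions", with HK-MoCA change from before to immediately after therapy as the other variable. The second is run only if the first is significant: "multiple regression will be conducted, with the eye-tracking parameters as predictors", with HK-MoCA change as the predicted variable.

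No age, education or baseline cognition term is named in any eye-tracking analysis. The fourth research question, under Aims and hypotheses to be tested, asks whether eye-tracking data are associated with treatment outcomes. The introductory section on eye-tracking goes a step further as background: "one may question if there is a causal relationship between changes in eye movements and treatment gain in MCI population".

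**The concern.** The comparison between arms is randomised, so covariates there mainly add precision. The eye-movement association is different. It compares people within one arm who happen to differ in how their gaze changes, and randomisation does not balance those people on anything. Participants who are younger, better educated or cognitively stronger at entry might adapt more to the headset tasks and also gain more on HK-MoCA. The two changes would then be correlated through that shared characteristic.

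Baseline cognition deserves separate mention. The predicted variable is a difference score on a test with a maximum of 30, so it depends on the starting value through regression to the mean and limited room at the top. If gaze change also varies with starting cognition, the association can arise from baseline alone.

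What is at stake is interpretation. The introduction raises eye movement as a possible biomarker of treatment response. This correlation and its follow-up regression are the only analyses that address the fourth research question. As specified, a significant result could not show whether eye movement carries information beyond characteristics the trial already records.

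**Working it through.** **Inputs from the protocol article**

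- 66 participants (Participants) allocated 1:1 (Randomization), so 66 / 2 = 33 in the IVR-CST arm.
- Planning attrition of 25% (Participants), so 33 × 0.75 = 24.75, or about 25 completers.
- Both variables are within-person changes: gaze from the first to the last three sessions, and HK-MoCA from before to immediately after therapy.
- The article gives no correlation of age, education or baseline cognition with either change. There is no stated figure to reproduce, so a range is assumed.

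**Set-up.** Let A be a shared characteristic such as age, X the eye-movement change and Y the HK-MoCA change, all standardised. Assume A correlates c with both, and that X and Y have no link other than through A:

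X = cA + √(1 − c²)·e₁,  Y = cA + √(1 − c²)·e₂

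The correlation between X and Y is then c × c = c², and the partial correlation given A is 0.

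**Result.** Simulation with 40,000 runs per cell, two-sided 5% level:

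| c (assumed) | Implied correlation c² | Unadjusted test significant, n = 25 | Unadjusted test significant, n = 33 | Adjusted for A |
|---|---|---|---|---|
| 0.2 | 0.04 | 5.4% | 5.7% | about 5% |
| 0.3 | 0.09 | 6.9% | 8.1% | about 5% |
| 0.4 | 0.16 | 12.0% | 14.5% | about 5% |
| 0.5 | 0.25 | 23.0% | 29.3% | about 5% |

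Up to c = 0.2 the effect is negligible. It becomes material only if the characteristic predicts both changes at about 0.4 or more.

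**Cost of adjustment.** The smallest significant correlation with k covariates is r = t / √(df + t²), where df = n − 2 − k and t is the two-sided 5% critical value.

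- n = 25, k = 0: df = 23, t = 2.069, r = 2.069 / √(23 + 4.280) = 0.396.
- n = 25, k = 3: df = 20, t = 2.086, r = 2.086 / √(20 + 4.351) = 0.423.
- n = 33, k = 0: df = 31, t = 2.040, r = 2.040 / √(31 + 4.160) = 0.344.
- n = 33, k = 3: df = 28, t = 2.048, r = 2.048 / √(28 + 4.196) = 0.361.

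Three covariates therefore raise the threshold by about 0.03 (n = 25) or 0.02 (n = 33).

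**The case against.** There is a serious case on the other side, and much of it stands.

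- **The aim is association.** The research question and the abstract speak of association and correlation, which an unadjusted correlation does test. With a shared cause the marginal correlation is truly c², not zero, so detecting it is no error for that question. This stands. The percentages above are false positives only for an association independent of the shared characteristic. A reader might infer that the test as planned has an inflated type I error; the documents do not support that without this condition. Nor do they plan a causal conclusion, because causality appears only as a background question.
- **Change scores remove stable effects.** An age or education effect on level alone cancels. Bias needs an effect on change in both measures, and the article gives no evidence for one. This stands, and it is why the range must include 0.2. It does not exclude differences in rate of adaptation or learning, or dependence on the starting score.
- **The section is not internally inconsistent.** A reader might infer that every outcome model is adjusted and that covariates were dropped here. That is not so: only the primary and secondary model carries them, and the eye-tracking session model names session number alone.
- **An article may leave covariates to a fuller plan.** This is true in general. Here, though, the article specifies the test, the sessions, the condition for going on, the predictors and the predicted variable. The comment concerns that stated choice.
- **Only sessions 1–3 and 12–14 enter the correlation.** A reader might count this as a further flaw. It is not one. A first-versus-last contrast is a legitimate summary, and the middle sessions are used in the across-session model. A slope over all sessions would assume linear change and equal noise across differently themed sessions.

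**Conclusion.** The point holds in limited form. The exploratory association is specified without covariates, in a non-randomised comparison of about 25 to 33 people. A significant result could therefore reflect age, education or baseline cognition rather than eye movement itself.

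The size cannot be determined from the documents. It runs from practically nothing at assumed correlations of 0.2 (5.4–5.7%) to 23–29% at 0.5, against about 5% after adjustment. These figures assume one shared characteristic, measured without error and equally correlated with both changes, and no independent link between the two.

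Severity is minor. The outcome is labelled exploratory, and no primary, secondary or feasibility conclusion depends on it.

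**What to change.** In the exploratory paragraph of Data analysis:

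1. Keep the unadjusted correlation, which answers the stated question of association.
2. Prespecify beside it a partial correlation, or a regression of HK-MoCA change on each eye-movement change, adjusted for age, education and baseline HK-MoCA. These match the characteristics named for the primary and secondary model.
3. State that any claim about eye movement as a marker of treatment response will rest on the adjusted result.

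The cost is three degrees of freedom per analysis, with education entered as a single term, and a few lines of wording. No new data are needed: age and education are already planned as covariates, and HK-MoCA is measured at week 1. With 25 to 33 participants the covariate list should stay at these three.
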